### Intervention adherence

A complier average causal effect (CACE) analysis to assess the impact of compliance on treatment estimates will be undertaken. CACE analysis allows an unbiased treatment estimate of, in this case, the incidence rate ratio of slips between the two groups in the presence of non-compliance with the shoes. It is less prone to biased estimates than the more commonly used approaches of per-protocol or ‘on treatment’ analysis as it preserves the original randomisation and uses the randomisation status as an instrumental variable to account for the non-compliance.

### Economic evaluation

The health economic evaluation will aim to establish the cost-effectiveness of slip resistant footwear in terms of preventing slips and falls. The economic evaluation will be undertaken in the form of a cost-utility analysis. It will be conducted from a societal perspective but will also distinguish costs that directly draw on the NHS budget. The trial Health Economist will write a detailed analysis plan prior to any analysis being conducted, which will be reviewed by the TMG and TSC and signed off by the Chief Investigator.

The analysis will estimate total net intervention costs, accounting for (i) implementation costs, primarily footwear purchase costs and (ii) avoided costs arising from the change in slip rates observed in the trial (reductions in lost working time due to absenteeism; medical treatment costs and compensation and legal costs).

We will use data collected during the trial on the consequences of slips, such as type of injury, duration of time off work and time spent in hospital, and model the effectiveness of the intervention beyond the 14-week time horizon of the trial. With the agreement of the participant, we will collect long-term follow-up data on the health state (EQ-5D-5L), healthcare resource use and absence from work, once a month after the 14-week final follow-up, from participants reporting an injury. If the participant reports an injury between randomisation but before the 14-week questionnaire then EQ-5D-5L data, information about whether the participants considers they have recovered from the injury and number of days ago they recovered will be collected. Data collection will stop when the injury has resolved, the participant no longer wishes to be contacted or the trial ends. The duration of modelling will depend on the expected lifetime of the footwear. We will gather information on this by asking 15 pilot participants to continue to wear their trial shoes for a further 6, 9 and 12 months (45 participants in total) and then assess the wear of these shoes. This will inform the modelling period used for the economic evaluation.

Table 1 provides an overview of data sources for each of the impacts that will be assessed in the economic evaluation. We will be able to complement this with data from the HSE’s Costs to Britain of workplace fatalities and self-reported injuries and ill health (‘Costs to Britain’) model, which is an established framework used to estimate the economic costs of workplace injuries and ill health for the purposes of annual National Statistics and regulatory impact assessments (http://www.hse.gov.uk/statistics/cost.htm).

**Table 1 T1:** Data sources for economic evaluation

Impact	Data required	Data source
Intervention costs		
Footwear purchase costs. At the societal level, the purchase of the intervention footwear will displace the purchase or wear of other footwear, so additional costs are likely to be minimal.	Pairs of footwear distributed, unit cost of footwear, effective lifetime of footwear.	Purchase costs already known. Data on effective lifetime of footwear to be collected during follow-up of 45 trial participants.
Managerial and staff time incurred in distributing footwear and communicating the intervention.	Given that the National Health Service (NHS) already has dress requirements and provides staff uniform, we expect that any additional staff time incurred in rolling out the slip resistant footwear will be negligible, so we do not propose to quantify this impact.	
Avoided costs (benefits)		
Loss of productivity/output due to worker absence. Loss of ‘production’ (in terms of services provided) to the NHS is likely to be minimised where hospitals recruit agency/bank staff to temporarily replace absent workers. The main costs to the NHS from worker absence would therefore be the costs of replacement agency/bank staff. At the societal level, a worker unable to work due to injury represents a reduction in the productive capacity of the economy.	Number of full-time equivalent working days lost due to slip-related injuries by type of worker. Average daily costs of agency/bank workers by role (including agency fees)	Trial data on reduction in slip injuries and full-time equivalent days lost, supplemented by the Labour Force Survey data on working days lost due to slips, trips and falls in the healthcare sector. Maximum rates for agency wages published by NHS improvement. Pay rates for bank staff published by NHS Trusts.
Staff sickness payments made to workers absent due to slip-related injury. This is not a cost at the societal level, since the payments are a transfer from employer (NHS) to employees.	Expected reduction in injuries resulting from slips in the NHS (using data from trial or modelled as discussed later in this protocol), the reduction in time off work associated with these avoided injuries, and NHS occupational sick pay policy (the trial excludes temporary/agency staff). Average daily staff costs (wages plus non-wage costs, such as national insurance and pensions contributions).	Trial data on full time-equivalent days lost as above. NHS occupational sick pay policy is set out in the NHS Terms of Conditions and Service Handbook. This will be used to model sickness payments based on time off work and staff wage rates. NHS staff wage rates by job band publicly available. Supplemented by data from the Annual Survey of Hours and Earnings where necessary and the ONS/Eurostat Labour Costs Survey (for non-wage costs).
Healthcare treatment costs incurred due to slip-related injuries.	Healthcare resource use, unit healthcare treatment costs.	Data on healthcare resource use to be collected in the study trial (14-week questionnaire). This will be costed using NHS Reference Costs unit costs database. Supplemented where necessary by published data on healthcare treatment costs for relevant injury types from published sources where available, and Health and Safety Executive (HSE) ‘Costs to Britain’ estimates of healthcare treatment costs for injuries.
Compensation (including legal) costs, arising from staff claims following injury under the NHS Liabilities to Third Parties Scheme (LTPS). At the societal level, the analysis will account for the transfer payment from staff claimants via the scheme.	Average compensation costs to NHS per case due to slip related injuries. This will be based on historical data as any claims from injuries sustained during the trial period are unlikely to be determined before the completion of the study.	NHS Resolution data on non-clinical compensation claims and payments under the NHS LTPS arising from slip-related staff injuries.
Administrative costs—reporting of slip injuries (RIDDOR), processing sickness payments, dealing with insurance and compensation claims.	Amount of staff time spent processing payments, claims, etc, plus wage rates of staff.	This is likely to be a small, if not negligible, impact. Could be valued using generic estimates from HSE Costs to Britain model of the typical costs per injury case.

The costing framework applied will ensure that transfers between groups are accounted for (eg, sickness payments), and that costs are not double-counted.

It is anticipated that avoided costs will be driven primarily by avoidance of slips resulting in injury. An estimate from Labour Force Survey (LFS) data shows that the injury rate from ‘slips, trips and falls’ in SIC 86 the ‘Human Health Activities’ is 0.46% (95% CI 0.38% to 0.55%, averaged 2008/2009–2016/2017). The rarity of injurious events means that it is likely we will need to model the impact of falls reduction on fall-related injuries; data collected from the trial study is likely to be insufficient to enable us to infer a relationship between slips and injuries. Given that the study is unlikely to provide statistically significant results on the change in the injury rate or types of injuries, a central scenario will be to assume that the change in injury rate is commensurate with the observed change in slip rate (ie, 30% fall in slips results in 30% fall in injuries, and a 30% reduction across all injury types/severities). To facilitate this analysis, we will complement the data collected during the survey with national data on slips reported under the LFS, held by HSE under licence from the Office of National Statistics. The LFS provides nationally representative data on self-reported injuries, including the severity of injuries, measured by time off work.

To enable a cost-utility analysis to be undertaken, we will collect EQ-5D-5L data from participants who report an injury and will produce health state profiles, which will be converted to utility scores using published National Institute for Health and Care Excellence (NICE)/EuroQol ‘standard tariffs’.^8^ We will validate this where possible with published studies on the health-related quality of life effects of comparable injuries. We will compare this with age/gender population level data of EQ-5D scores to derive the utility loss associated with slip-related injuries. This will enable the standard cost per quality-adjusted life year (QALY) measure of cost-effectiveness to be derived. We feel it too onerous and costly to collect EQ-5D from the total trial population as is usual in a trial-based economic evaluation, as the vast majority of the participants are healthy and working, will not have an injury and will return a high utility score. It is proportionate therefore to use existing general population data from published sources.

Two ‘threshold’ tests will be undertaken:The change in injury rate required to achieve a cost per QALY equal to the NICE threshold of £20 000 to £30 000.The ‘break-even’ change in injury rate from the perspective of NHS costs.

The analysis will produce the following results:Total net intervention costs (implementation costs minus avoided costs) to the NHS and to society.Cost per QALY gained, from both NHS budget and societal perspective.Threshold tests, as above.

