### Secondary outcome measures for the SSHeW trial

Secondary outcomes will be self-reported by the participant and collected via text or questionnaires sent at baseline, 14 weeks or following the report of the first slip or an injury. They include:The incidence rate of falls resulting from a slip in the workplace over 14 weeks.The incidence rate of falls not resulting from a slip in the workplace over 14 weeks.Proportion of participants who report a slip over 14 weeks.Proportion of participants who report a fall over 14 weeks.Proportion of participants who report a fracture over 14 weeks (numbers permitting).Time to first slip.Time to first fall.EuroQol EQ5D-5L.Cost-effectiveness.

Other important information collected includes:Reason for slip/fall, location of fall, type of flooring and if wet or dry, consequence of slip/fall, that is, superficial wound (bruising sprain, cut, abrasions), fractures and type of fractures; severity of fall; type of footwear worn at time of slip/fall.Number of days off work, due to the slip or fall.Footwear worn at time of first slip.Number of hospital admissions.Number of days in hospital.Compliance and reasons for non-compliance.Any minor injuries resulting from ill-fitting shoes.Style of footwear usually worn.Wear on soles of 45 intervention shoes at 6, 9 and 12 months postrandomisation.Slip resistance of a sample of the current footwear worn by NHS staff.

Copies of the data collection forms are available from the corresponding author.

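### The economic model targets slip-related injuries but names data that pool slips, trips and falls, and has no step isolating the share to which the slip reduction applies.

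*Protocol article*

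**What the plan says.** All of this is in the protocol article.

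- **Rule.** Under Economic evaluation, after Table 1, "a central scenario will be to assume that the change in injury rate is commensurate with the observed change in slip rate". The example given is that a "30% fall in slips results in 30% fall in injuries, and a 30% reduction across all injury types/severities".
- **Injury rate.** The same paragraph quotes one injury rate, from the Labour Force Survey (LFS): "the injury rate from ‘slips, trips and falls’ in SIC 86 the ‘Human Health Activities’ is 0.46% (95% CI 0.38% to 0.55" (the upper limit is also a percentage).
- **Days lost.** In Table 1 the quantity required is "Number of full-time equivalent working days lost due to slip-related injuries by type of worker". The source is trial data, "supplemented by the Labour Force Survey data on working days lost due to slips, trips and falls in the healthcare sector".
- **Description of the survey input.** After stating the scenario, the text says "we will complement the data collected during the survey with national data on slips reported under the LFS".
- **What the trial measures.** Under Outcome measures, a slip is a loss of traction, whether or not a fall follows. A separate secondary outcome is "The incidence rate of falls not resulting from a slip in the workplace over 14 weeks".

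**The concern.** The multiplier and the quantity it may be applied to do not cover the same events. The multiplier is the change in slips, which are loss-of-traction events only. The injury rate and the days-lost source, as named, also include trips and other falls. The trial keeps slip and non-slip falls apart as outcomes, but the central scenario as described makes no such separation.

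If the pooled inputs go into the model as named, the central case assumes that trip and other non-slip injuries fall by the same percentage as slips. The trial may or may not show that, and nothing in the document supports assuming it beforehand. The error would favour the footwear and would carry through to avoided injuries, days lost, avoided costs, QALYs gained and cost per QALY. The Introduction says that the findings are meant to inform the business case for buying such footwear, so the central estimate will be used.

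**Working it through.** **Plan's own figure.** The section reports no economic result to reproduce. The 30% in its example equals the design effect under Sample size: 1 − 0.07/0.10 = 30%.

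**Inputs**
- Pooled injury rate: 0.46% (0.38% to 0.55%), Economic evaluation; treated here as annual.
- Reduction in slips: R = 30%, the plan's example.
- Share of pooled injuries caused by slips: s. Not in the documents; 80%, 60% and 40% are assumed for illustration.
- Relative reduction in non-slip injuries: r. Not known in advance.

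**Step 1: the rule applied to the pooled rate.** 0.0046 × 0.30 = 0.00138, or 1.38 injuries avoided per 1000 workers. Over the stated confidence interval this is 1.14 (0.0038 × 0.30) to 1.65 (0.0055 × 0.30).

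**Step 2: the rule applied to slip-caused injuries only (r = 0).** Avoided per 1000 = 1.38 × s; overstatement = 1/s.

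| Assumed s | Avoided per 1000 | Reduction in pooled injuries | Overstatement |
|---|---|---|---|
| 80% | 1.10 | 24% | 1.25 |
| 60% | 0.83 | 18% | 1.7 |
| 40% | 0.55 | 12% | 2.5 |

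**Step 3: some effect on non-slip injuries.** The pooled reduction is sR + (1 − s)r. With s = 50% and r = 10% it is 0.15 + 0.05 = 20%, so 30% overstates by 1.5. With r = 30% there is no overstatement. Hence 1/s is the upper bound for r between 0 and R.

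**Step 4: cost per QALY.** Let C be the implementation cost, and B and Q the avoided costs and QALYs under the pooled rule. The pooled result is (C − B)/Q. If only the slip share responds it is (C − sB)/(sQ). Their ratio is (C − sB)/[s(C − B)], which is at least 1/s because C − sB ≥ C − B. This requires C − B > 0. If the footwear is cost-saving, the ratio has no such reading.

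**Step 5: can the trial supply s?** From injuries, hardly: 2200 × 0.0046 × 14/52 ≈ 2.7 expected per arm. From falls, yes, roughly. At the 5.5% fall risk under Sample size and 2200 × 0.8 = 1760 followed, about 97 control participants fall. A 50% share would then have a standard error of √(0.25/97) ≈ 5 percentage points (simple binomial, one fall per faller).

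**Step 6: which arm?** If the control share is 50%, slips fall by 30% and other falls do not change, both arms together give (0.50 + 0.35)/(1.00 + 0.85) = 46%. Pooling the arms would therefore bias the share downwards if the shoes work; the control arm alone avoids this.

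**The case against.** The strongest defence is that the model is meant for slip injuries throughout. Table 1's sick-pay row, which points forward to the modelling, speaks of injuries that result from slips. The days-lost, treatment and compensation rows, and the later text on utility loss, all refer to slip-related injury. The survey input is once described as data on slips. The 0.46% is followed at once by a remark on rarity, so it may be there only to explain why modelling is needed. The wording on types and severities can mean kinds of injury and time off work, not trips.

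Much of this stands. A reader might infer that the plan definitely multiplies 0.46% by the slip reduction and so credits the shoes with preventing trips. The documents do not support that, because no sentence makes 0.46% the base. Nor do they support saying that the model ignores trial evidence: Table 1 puts trial data on slip injuries and days lost first, with the survey as a supplement.

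What survives is the mismatch. The survey figures in the Introduction and Economic evaluation, and the days-lost source in Table 1, are all pooled. If a slip-coded series exists, it is not named.

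Three further defences are weaker.
- A health-economics plan is promised, but the point concerns a rule and sources already stated, and that plan is where to correct them.
- The two threshold tests show what injury reduction is needed but do not correct the central estimate. At s = 50%, a 30% fall in slips is a 15% fall in pooled injuries, so a pooled break-even of, say, 20% would wrongly look met.
- The shoes may also reduce non-slip falls, which the secondary objectives list. That is a question for the trial, not grounds for assuming the full slip effect.

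**Conclusion.** The point holds as a mismatch between the stated target and the named data, with no step linking them. It does not establish that the final model will be wrong.

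If the pooled inputs are used as named and non-slip injuries fall by less than slips, avoided injuries, and the costs and QALYs that scale with them, are overstated by up to 1/s: 1.25, 1.7 or 2.5 times at the assumed shares. Cost per QALY is understated by at least 1/s when non-slip injuries do not respond, and only while net cost stays positive. The direction is clear under these conditions. The size is not, because the documents give neither s nor the effect on non-slip injuries.

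**What to change.** State in the health-economics analysis plan that the slip rate ratio applies only to the slip-attributable part of the survey injury rate and days lost.

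- **Source of the share.** Use slip-coded survey data if available. Otherwise use the control-arm split of falls (or injuries, if numbers allow) into those resulting and not resulting from a slip. Call it a proxy: the split of falls need not equal the split of injuries, and a slip can injure without a fall.
- **Central case.** Assume no effect on the remaining injuries.
- **Sensitivity analysis.** Vary both the slip share and the non-slip effect, the latter informed by the trial's non-slip fall outcome. Keep the version that reduces all injuries equally as an optimistic scenario.
- **Threshold tests.** Say whether the required injury reduction refers to slip-related or pooled injuries.

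The trial already collects the fall data, so the cost is wording and a little more modelling. The downside is a less favourable central estimate.

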### Qualitative analysis

All interviews will be audio-recorded digitally and transcribed verbatim. A computer package such as ATLAS-ti or NviVo may be used to manage the data. Initially following transcription the data will be analysed using the constant comparison method through thematic coding of the data.^9^ Coding will take place using a combination of prior themes and emergent themes. Negative cases will be actively sought throughout the analysis and emerging ideas themes modified in response.^10^ Integration of these interview findings with the quantitative data collected in the acceptability questionnaire will be done using a ‘triangulation protocol’.^11^ This will be done at the data interpretation phase,^12^ the data having first been analysed independently. A convergence matrix will be created to display the quantitative and qualitative findings to maintain a sharp focus on the relevance of findings to evaluating the mechanisms of impact for the intervention.

### Trial monitoring

The day-to-day management of the study will be monitored by the Trial Management Group. An independent Trial Steering and Data Monitoring Committee will be set up. The committee will meet at least annually or more frequently if the committee requests. Site monitoring will not be undertaken on behalf of the Sponsor since the eligibility for the study is undertaken by review of participant’s self-reported data by researchers based at the YTU and consent is taken via the post.

## Ethics and dissemination

### Ethics

All participants will give written informed consent prior to entry to the study and will be made aware that participation is strictly voluntary. Further consent will be obtained for the qualitative interviews and for testing of footwear for slip resistant properties. Participants may withdraw from the study at any time.

### Dissemination

The results of the study will be disseminated through peer-reviewed journals and in the NIHR PHR monograph. The results will also be presented at health and safety conferences, such as The Royal Society for the Prevention of Accidents; Institution of Occupational Safety and Health and The National Examination Board in Occupational Safety and Health. The HSE will disseminate the findings of the study through their website (www.hse.gov.uk), through direct communications to interested parties such as Health and Safety Managers and via the ‘GRIP’ scheme. The results will also inform the contents of the ‘Slips and Trips—Falls Prevention’ training course run by the HSE. A short summary of the results of the study will be produced, which could be distributed to all trial participants and hospital managers at participating trusts.

### Patient and public involvement

Our patient and public representatives were identified from members of the Cheshire and Wirral Partnership’s NHS Foundation Trust’s Ward Management Task and Finish Group and staff employed by this NHS Trust. NHS employees have helped develop the design and conduct of the study, by providing feedback on the grant application submitted to the funder. They advised on the suitability of the proposed footwear, use and wording of text messages, the method to collect data and the frequency and duration of contacts to ensure an acceptable level of burden and trial documentation. A patient and public involvement representative forms part of the TSC to guide the conduct of the study. A summary of the findings will be made available to trial participants.

### Studies within trials

In addition to the main SSHeW study, one ‘Study within a Trial’ is being conducted.

